## Abstract

**Objective:**

Non-verbal behaviors (NBs) of caregivers affect pain reports and placebo effects. However, little experimental research has systematically examined the caregivers' NBs. This study protocol and preparatory study report a systematic manipulation of experimenters' NBs to investigate pain report and placebo effects.

**Methods:**

We propose an experiment in which videotaped experimenters (VEs) conduct a pain stimulation and a placebo treatment study. The VEs express one positively enhanced NB and keep the other NBs neutral. Participants will be randomized to either the positive facial expressions (+FE), tone of voice (+TV), body movement (+BM), or neutral NBs (i.e., neutral condition; NC) of the VEs. As a preparatory study for proof of concept, two groups of NB coders from Norway and the USA separately rated the degree of NBs (eye contact, body postures and movements, and tone of voice), and impressions of dominance and being in charge, positivity, and expressivity from each NB video. The NB videos had construct validity and reliability. The +BM and +FE were rated as more dominant and in charge than the +TV and the NC. The +FE and +BM were rated as the most positive and expressive NBs, respectively.

**Expected results:**

+FE will have the largest placebo effects on pain and stress levels. However, transmitting the NBs to patients by VEs is challenging. Moreover, controlling for the effects of research assistants present in the testing room is challenging.

**Discussion:**

We propose that caregivers' NBs affect pain reports and placebo effects. Moreover, different NBs elicit different impressions, and a better understanding of the role of caregiver NBs requires more rigorous investigations. Lastly, aiming to investigate the caregiver NBs, the varying degrees of micro-NBs and their effects on the formation of impressions should be considered.

## Introduction

Placebo analgesia, the reduction in pain due to the administration of a medically inactive element (Amanzio and Benedetti, 1999; Vambheim et al., 2021), is caused by positive expectations about a treatment, which is thought to be partly due to the treatment setting, indicating that an effective treatment has been administered (e.g., Miller and Kaptchuk, 2008). Placebo effects are embedded in all kinds of treatments and placebo-controlled trials (Benedetti et al., 2014). Verbal information modulates treatment expectations (Flaten et al., 2006); however, verbal suggestion is just one source of information for patients, and contextual factors, such as the clinic, the doctor–patient relationship, and the caregiver's gender (Levine and De Simone, 1991) and their characteristics (Kállai et al., 2004; Howe et al., 2017), contribute to treatment outcomes and placebo effects (Daniali and Flaten, 2019).

Among these, the non-verbal behaviors (NBs) of caregivers are shown to influence treatment outcome and placebo effects (Benedetti et al., 2014; Czerniak et al., 2016; Daniali and Flaten, 2019). A considerable amount of emotions, thoughts, and feelings are conveyed by NBs (DePaulo and Friedman, 1998), and our NBs can align or contradict with our verbal messages (e.g., Ekman, 1965; Jacob et al., 2013). Even the absence of NBs (i.e., neutral expressions) may convey an impression (e.g., negativity or disengagement) (Said et al., 2009; Knapp et al., 2013).

NBs can be categorized into macro-level and micro-level. Macro-level NBs, also called impressions, are the result of a combination of a series of micro-level NBs (Ambady et al., 2000; Matsumoto, 2006a,b; Burgoon et al., 2011). Micro-level NBs are specific NBs such as smiling, direction of gaze, and limb movements that can generate macro-level NBs (Ambady et al., 2000).

Both micro- and macro-level NBs can be either positively or negatively valenced. Positive NBs are more immediate and reduce the actual or psychological distance between two interactants (Mehrabian, 1969), and negative NBs imply a negative feeling or attitude or increase the actual or psychological distance between the two interactants. Such positivity and negativity in NBs are typically compared against the neutral NBs, which reflect neither positive nor negatively valenced feelings or attitudes.

Patients draw impressions from their caregivers' NBs (e.g., how friendly, competent, warm, empathic, positive, etc. the doctor is), which in turn impact the treatment outcomes. Kraft-Todd et al. (2017) showed that when caregivers' photographs displayed enhanced eye contact, leaning forward, and smiling, participants rated higher impressions of empathy and warmth compared to when the counterpart NBs were displayed to participants. A review by Daniali and Flaten (2019) showed that several positive NBs (e.g., smiling, enhanced eye contact, positive tone of voice, and close proximity to the patient) of caregivers lowered clinical and experimental pain and increased placebo effects, and conversely, negative NBs (e.g., lack of smile, no eye contact, etc.) increased pain and nocebo effects. In addition, Czerniak et al. (2016) also showed that when the clinician displayed positive body postures, escorted the patients, had longer eye contact, and smiled more, the patients could withstand cold pain longer. The positive NBs of the caregivers have also been shown to reduce negative emotions (e.g., van Osch et al., 2017).

However, one issue still not thoroughly investigated is which NBs have the most salient effect on pain reports and placebo effects. To reliably investigate the caregivers' NBs, the NBs must be defined and measured in a systematic and replicable manner. This is a challenging task, as there is no NB dictionary to define and measure NBs (Blanch-Hartigan et al., 2018). This is partially why in most of the available literature, an unspecified group of NBs has been simultaneously manipulated, making the results conflated and unable to show the role of specific NBs (e.g., Kaptchuk et al., 2008).

## Experiment outlook

To answer this, we designed an experiment in which the NBs of the experimenters were separately enhanced, recorded, and then tested on pain reports and placebo effects. A videotaped experimenter (VE) guided a pain experiment and introduced a treatment (a placebo) while expressing specific NBs. Four NB conditions were developed. In three conditions, one NB was positively enhanced, and in the fourth condition, all NBs were neutral. The conditions were positive facial expressions (+FE), tone of voice (+TV), body movements (+BM), and neutral conditions (NCs). This article describes the experiment protocol and the procedures to design and validate the NBs of VEs.

## Experiment protocol

General aims were as follows: (1) Positively enhanced NBs will have a larger reduction in pain and placebo amplitude compared to the NC, (2) the +FE will have the largest reduction in pain and placebo effect compared to other NB groups, (3) larger reduction in pain will be associated with lower stress levels (both physiological and subjective) and (4) the +FE will have the lowest stress level compared to other NB groups.

## Methods

### Participants

Eighty healthy volunteers (40 females and 40 males) between the ages of 18 and 45 will be recruited. The age was limited to a younger age range, as aging might affect pain sensitivity (Yezierski, 2012). Participants will be randomly assigned to four groups (20 participants each group), each with 10 males and 10 females. Each participant will be paid 200 NOK (approximately 20 USD). A history of severe psychiatric disorder, chronic pain, injuries or scars on the right arm, pregnancy, or use of prescription drugs (except birth control pills) will result in exclusion. Participants will be requested not to drink alcohol 24 h prior to the experiment and abstain from large meals, nicotine, caffeine, or energy drinks 3 h prior to the experiment.

### Questionnaires

*Pain intensity and pain unpleasantness* will be rated on an 11-digit numeric rating scale (NRS) as described by Price et al. (1983).

*Stress and arousal* are assessed before and after the stimulations, by the Short Adjective Check List (SACL; Mackay et al., 1978): two adjective pairs, each rated on a scale from “0” to “10.” Stress is measured by asking participants to rate how “relaxed” or “tense,” or how “calm” or “nervous” they are, on a scale from “0” to “10.” Arousal will be assessed the same way on the scales of “sleepy” or “awake,” and “tired” or “energetic.” SACL has been used in several similar studies (Lyby et al., 2010; Bjørkedal and Flaten, 2011; Vambheim et al., 2021).

*CARE*. Three items (items 1, 6, and 8) from the 10-item Consultation and Relational Empathy (CARE) (Crosta Ahlforn et al., 2017) are selected to assess the satisfaction of the VEs.

*Expected efficacy*. After receiving the placebo cream and before the pain stimulation in the conditioning and post-test phases (see Procedure), participants will be asked to rate how much they expect the cream will reduce their pain intensity on an 11-digit NRS.

*Prior experience* with the cream. Participants will be asked whether they have had any former experience with thermal pain-relieving creams. If the answer is yes, they will be asked to rate the efficacy of the cream on an NRS (Aslaksen and Flaten, 2008).

*The Big Five Inventory-Short Form (BFI-10)* (John et al., 1991) and the *Fear of Pain Questionnaire III (FPQ III)* (McNeil and Rainwater, 1998) will be filled out before the experiment begins.

### Psychophysiological measurements

Cardiac activity will be recorded using the MP150 BIOPAC system. The electrocardiogram (ECG) is used to compute heart rate variability (HRV) and heart rate (HR), which indicate the contributions of sympathetic and parasympathetic activity to the heart (Appelhans and Luecken, 2008; Aslaksen and Flaten, 2008). The ECG will be continuously recorded during the stimulations from one electrode attached to the upper part of the left chest and two electrodes attached to the lower ribs on both sides. The signals will be sampled at 1000 Hz with the BIOPAC Acqknowledge 3.7.1 software (BIOPAC Systems Inc., USA).

### Pain induction system

Thermal pain will be induced by a 30 × 30 mm thermode (metal plate) controlled by a Pathway ATS (Medoc) (TSA II, Medoc, Ramat Yishai, Israel).

### NB scenarios

Four NB scripts (+FE, +TV, +BM, and NC) were designed, of which three (+FE, +TV, and +BM) had one positively enhanced NB and the other as neutral as possible. Positive NBs were defined as NBs that conveyed a positive feeling to the observer (Mehrabian, 1969). Neutral NBs were defined as NBs that did not convey a specific emotion to the observer and were significantly less positive than positive NBs (Blanch-Hartigan et al., 2018). In the +FE, the VE expressed frequent smiling and nodding, enhanced eye contact (longer than a total of 5 min), more expressive eyebrow, lip, and cheek muscle movements, and more nodding. In the +TV, the VE spoke with a calm, friendly, warm, and positive tone of voice. In the +BM, the VE leaned toward the camera more frequently (to imply closer proximity to the participant) and had elaborate and expressive hand movements such as indexing, counting with fingers, and indicating sizes, timelines, and shapes with hands. Other than the positively enhanced NBs, the other NBs were kept as neutral as possible. In the NC, all NBs were kept neutral; therefore, the VE showed a flat face without smiling and without enhanced eye contact, used a monotonous tone of voice, and displayed a straight body posture without moving the hands or the torso (see Figure 1).

**Figure 1 F1:**
[figure not shown]
NB conditions. **Top left**: positive facial expressions (+FE); **top right**: positive body gestures (+BM); **bottom left**: neutral condition (NC); **bottom right**: positive tone of voice (+TV). Furthermore, as depicted in the **bottom right** panel, all conditions were acted by all three actors. With permission from actors.

### Videotaped experimenters

Three Norwegian female professional actors in the age range of 26–32 played VEs. The actors were typecast to fit a usual health personnel stereotype (Mercer et al., 2008), wearing a white lab coat and light makeup. All NB conditions were played by all three actors (Figure 1). Before recording, each actor received about 10 h of training with the playscripts. VEs have been used in previous studies (Hunter et al., 2014; Ruben et al., 2017). To ascertain the validity of NBs, all video conditions were played by all actors.

### Research assistants

Three female assistants will conduct the experiment. Every assistant will test 26–28 participants. Using written instruction, the assistants will be trained to conduct the experiment and how to control their verbal and non-verbal interactions. The assistants then run a simulation experiment with the first author (HD), and if successful, they will start testing the participants.

### Blinding of assistants

Two types of information about the creams will be given to the assistants. For half of the participants, the assistants will be told that that half of the creams are active pain-relieving creams and the other half placebo creams; therefore, there will be a 50% chance for each participant to receive an active pain-relieving cream; however, you (the assistant) would not know which participant receives which cream. These assistants are hereafter called uncertain information assistants (UI assistants). For the second half of participants, the assistant will be told that all creams are active pain-relieving creams; therefore, all participants will receive the active pain-relieving cream. These assistants are hereafter called certain information assistants (CI assistants). The effects of the type of information told to assistants will be tested under the following exploratory hypotheses: (5) CI assistants will elicit larger placebo effects than UI assistants. (6) Participants tested with CI assistants will have lower stress and arousal than participants tested with UI assistants.

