### Conditioning of assistants

To strengthen the belief about the effectiveness of the creama, conditioning will be performed on CI assistants with an active pain-relieving cream (lidocaine 5%), identical to the placebo. To do so, the assistants will undergo a conditioning with two phases, first without the lidocaine cream and then with the lidocaine cream. The stimulation will be a thermal stimulation, starting at 32^o^C, with an increase rate of 0.25^o^C /s, ascending until the assistant reports a pain intensity of “5” on an NRS. For the second time, a 5% lidocaine cream will be administered on the assistants' forearms with a 15-min waiting time for the cream to take effect, and then, an identical ascending thermal stimulation will be induced until the assistant reports a pain intensity equal to “5.” Afterward, the results of both pain stimulations will be shown to the assistants to prove that the cream made them tolerate a higher stimulation.

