### Design

We propose a mixed design with four Groups (+FE, +TV, +BM, and NC; as between factors) × 3 Timepoints (first at 30 s, second at 2 min, and third timepoint at 4 min of the stimulation), with the covariate effects of participant sex with two levels, and the knowledge of the assistants with two levels (CI and UI).

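### Three assistants with one role each cannot produce the stated UI and CI halves, and the CI/UI contrast is confounded with assistant under fixed roles, or with time if assistants switch from UI to CI

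*Protocol article*

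**What the plan says.** All references are to the Protocol article.

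- Participants: "Eighty healthy volunteers (40 females and 40 males) between the ages of 18 and 45 will be recruited".
- Research assistants: "Three female assistants will conduct the experiment", and "Every assistant will test 26–28 participants".
- Blinding of assistants, on the uncertain information: "For half of the participants, the assistants will be told that that half of the creams are active pain-relieving creams". On the certain information: "For the second half of participants, the assistant will be told that all creams are active pain-relieving creams". The section then attaches the label to the person and not to the session: "These assistants are hereafter called certain information assistants (CI assistants". Hypotheses 5 (larger placebo effects with CI) and 6 (lower stress and arousal with CI) are called exploratory.
- Conditioning of assistants: "conditioning will be performed on CI assistants with an active pain-relieving cream". The assistant is then shown both of her own results as evidence that the cream works.
- Design: four NB groups by three timepoints, with participant sex and "the knowledge of the assistants with two levels (CI and UI") as covariates. Neither assistant identity nor test order is among the terms.
- Expected limitations: the article accepts that the assistants' presence may affect the results, and answers this by analysing the information they were given.

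**The concern.** The information factor is described in two ways that do not obviously agree: as a property of half the participants, and as a property of the assistant. The number of assistants and their stated workload decide whether both can hold. If they cannot, some assistants must work under both instructions, and the order then matters, because conditioning with an active cream is not readily undone.

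At stake is what hypotheses 5 and 6 can show. Both are worded as effects of what the assistant believes. If that belief coincides with who the assistant is, or with when in the study she is testing, a CI/UI difference could come from any of these. The listed model offers no term to separate them. The assistant moves the thermode, applies the cream and changes the temperature, so differences between three people are plausible on the article's own account.

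**Working it through.** **1. The plan's own figures.** Three assistants at 26–28 each cover 3 × 26 = 78 to 3 × 28 = 84 participants, so a total of 80 fits. The only loads that sum to 80 are 26 + 26 + 28 and 26 + 27 + 27. Half of 80 is 40.

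**2. One role per assistant.** One assistant covers 26, 27 or 28 participants and the other two cover 54, 53 or 52. The possible splits are 26:54, 27:53 and 28:52, and 40:40 is not among them.

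**3. At least one assistant under both instructions.** Halves of 40 become possible. Examples are 27 UI + 27 CI with the third assistant's 26 split 13/13, or all three switching at 13 or 14 participants (13 + 13 + 14 = 40).

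**4. Fixed roles: error of a test that ignores assistant.** Take 27 v 53, with total variance 1 and an assumed intraclass correlation ρ for assistant. The ratio of the true variance of the contrast to the variance the test assumes is

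[ρ(1 + 1/2) + (1 − ρ)(1/27 + 1/53)] / (1/27 + 1/53), with 1/27 + 1/53 = 0.0559.

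- ρ = 0.01: (0.0150 + 0.0553)/0.0559 = 1.26
- ρ = 0.05: (0.0750 + 0.0531)/0.0559 = 2.29
- ρ = 0.10: (0.1500 + 0.0503)/0.0559 = 3.58

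Type I error = 2·P(Z > 1.96/√ratio) = 0.08, 0.20 and 0.30. A simulation of a two-sample t-test (100,000 runs) gives 8%, 20% and 31%.

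**5. The same simulation for the other schedules,** at ρ = 0.01, 0.05 and 0.10:

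- two fixed, one split 13/13: 7%, 15%, 25%
- all three switching: 5.0%, 4.6%, 4.3%

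**6. All switching from UI to CI: drift.** Let the outcome drift linearly by T (in SD units) over the study. The first half averages T/4 and the second 3T/4, so the CI/UI contrast is biased by T/2. For assumed T of 0.2, 0.4 and 0.6, the spurious standardised difference is 0.10, 0.20 and 0.30. A 40 v 40 t-test then rejects in 7%, 14% and 26% of trials with no effect of information.

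**7. Can a session-order covariate remove this?** With order x uniform on 0 to 1 and phase h = 1 in the second half, cov(x, h) = 3/8 − 1/4 = 1/8, var(x) = 1/12 and var(h) = 1/4. The correlation is (1/8)/√(1/48) = 0.87. The variance inflation is 1/(1 − 0.75) = 4, so the CI/UI standard error roughly doubles.

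**The case against.** The strongest reply is that the Blinding section allocates information by participant, and its sentence on the uncertain information speaks of the assistants in the plural. On that reading all three work under both instructions, 40:40 is reachable, and ignoring assistant does not inflate the error rate. This stands. A reader might infer that equal halves are impossible, or that the CI/UI test is anticonservative whatever the schedule. The documents support neither, and the 0.08 to 0.30 figures belong to fixed roles only.

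It is also fair that no section states an order. The phrase about the second half may simply mean the other half. The lidocaine conditioning makes UI before CI the natural sequence, but that is an inference. Counterbalancing would reduce the time problem, although three assistants cannot be divided evenly over two orders.

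The hypotheses concerned are labelled exploratory, and the assistants' presence is acknowledged as a limitation. Both points hold and limit the consequence. They do not turn a confounded contrast into an effect of information, and the article's answer to the limitation is that same contrast.

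Finally, an article may leave the assistant schedule and the allocation list to the full protocol. Their absence alone is not the point here. The point is that the stated workload and the stated halves fit together only if an assistant changes role, and that the Design section does list its model terms, with assistant not among them.

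**Conclusion.** The concern holds in conditional form. The stated workloads and the stated halves conflict if each assistant keeps one role, and agree only if at least one works under both instructions.

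- **Fixed roles:** CI/UI is one assistant against two, and no analysis can separate it from identity. Type I error is about 0.08, 0.20 and 0.30 at assumed intraclass correlations of 0.01, 0.05 and 0.10.
- **All three switch:** there is no such inflation, but if the order is UI then CI, the contrast absorbs half of any linear drift over the study.
- **Only one switches:** both problems are present in part.

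The intraclass correlations and drifts are assumptions. The article gives neither.

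A reader might go further and conclude that the NB comparisons (aims 1, 2 and 4) are biased. The documents do not show this. Those groups are randomised, and nothing indicates that assistants or information are spread unevenly over them, although the article does not say that they are balanced. What is affected is the interpretation of exploratory hypotheses 5 and 6.

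**What to change.** 1. Reconcile Research assistants, Blinding of assistants and Conditioning of assistants: state which assistant works under which instruction, for how many participants and in what order.
2. Balance the NB groups over assistant and information phase in the allocation list.
3. Add assistant (three levels) as a fixed factor in the NB-group models. Her identity is known for every session.
4. Estimate CI minus UI within assistant only where assistants switch. Under fixed roles the assistant factor absorbs CI/UI completely, so the two cannot be fitted together. If only one assistant is split 13/13, she alone informs the estimate, and its standard error is √(40/13) = 1.75 times that of a 40 v 40 comparison with the same residual variance.
5. Use session order only as a sensitivity analysis, because under UI then CI it roughly doubles the CI/UI standard error.
6. Report hypotheses 5 and 6 as descriptive associations and not as effects of the information given.

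The cost is 2 degrees of freedom and a weaker claim for two hypotheses already labelled exploratory. With main effects only, the between-participant residual falls from 80 − 1 − 3 − 1 − 1 = 74 to 72.
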